#### Secondary outcome measures

2.8.2

Table 1 presents the details of secondary outcome measures. These information comprehensively reflect effectiveness and safety of drainage, and difficulties in cholecystectomy.

**Table 1 T1:**
[figure not shown]
Secondary outcome measures.

### Participant timeline

2.9

Please see Table 2.

**Table 2 T2:**
[figure not shown]
Participant timeline.

### Sample size

2.10

The sample size calculation is based on the primary outcome-the pain score after drainage. According to the research by Jang et al,^[18]^ using the method provided by Luo et al^[19]^ and Wan et al,^[20]^ the median post-procedure pain score in the PTGBD group was 5.4 ± 3.1. And the mean visual analog score of post-procedure pain in the ENGBD group was 1.3 by Itoi et al.^[9]^ Using a theoretical sample size for two-sample design, nine participants are needed in each group with 80% power and a 5% significance level. Allowing for a 10% loss to follow-up, we plan to recruit 22 patients (11 in each group).

### Recruitment

2.11

The recruitment would last 20 months, which began in June 2018. This duration was estimated based on the number of admissions for surgical high-risk AC patients at the team in previous 2 years. To achieve adequate participant enrollment, relevant work on the study would be performed around the clock, including nights and weekends as routine clinical practice.

### Allocation sequence generation and randomization

2.12

The randomization numbers were generated by statistician using computer program with 1:1 allocation, stored and encoded 20 sealed, opaque envelopes independently. When a participant meets inclusion and inclusion criteria, two volunteers first record the name and the code of the next unopened envelope, then open the envelope and sign their names. At last, the treatment assignment would be sent to the attending physicians, which could get only one allocation at a time after all pre-drainage preparations were completed, including the evaluation of patients and informed consent of participants.

### Blinding

2.13

This is an open-label, unblinded trial for patients and physicians because of the nature of the intervention (position and shape of drainage tube). However, the investigator of collecting secondary outcomes, the assessor of clinical and biological data in charge of statistical analyses and outcome assessment will be masked as to the subjects assigned group.

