### Interventions

2.7

A systematically trained experienced attending physician assesses that once evidence of gallbladder drainage is available, all patients eligible for inclusion were informed fully of written informed consent, then would be randomly assigned to the interventional group (ENGBD) or to the reference group (PTGBD). Of course, risks and benefits associated with surgery would be routinely communicated and agreed in writing.

The experimental group patients are sedated by intravenous administration of sufentanil and propofol, then selective bile duct cannulation, a 0.025- or 0.035-inch guidewire is advanced into the cystic duct and subsequently into the gallbladder, withdraw the catheter, a 5Fr naso-gallbladder catheter is inserted into the gallbladder along the guidewire. PTGBD is guided by ultrasound, an 18-gauge needle is inserted into the gallbladder, a 0.035-inch guidewire is coiled into the gallbladder and a 9Fr dilator expands the skin, then an 8Fr 20 cm catheter is placed.

When ENGBD was technically unsuccessful or clinically ineffective, endoscopic nasobiliary drainage (ENBD), PTGBD and EUS-GBD were used as alternative procedures. The patients of inclusion would be given appropriate and quality treatment at anytime, in order to reduce waiting and improve adherence. Properly trained volunteers would accompany patients on key treatments, such as ERCP and PTGBD, extubation, LC, etc. This not only improves adherence, because of the convenience to patients, but also monitors adherence to a certain extent.

All patients of inclusion would be assessed by the attending physician in accordance with recent guidelines for AC management, including sufficient infusion, maintenance of electrolyte balance, antibacterial agents, the monitoring of respiratory and hemodynamics, correction of acidosis and complications.

In particular, there is no strict recommendation for extubation time, ENGBD group would extubate when the bile in the naso-gallbladder tube becomes clear, which is approximately 4 days after the drainage based on our experience. PTGBD group extubate after more than 2 weeks due to fistula formation. Also, no consensus has been reached about the optimal timing of LC after drainage. Because most studies^[15–17]^ figure out the short interval increases intraoperative difficulty, we require all patients to undergo cholecystectomy 3 months after drainage, so that edema and inflammation around the gallbladder subsided completely.

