#### Collection, management

2.14.1

All data are prospectively collected and managed by the well-trained research volunteers.

The baseline data would be collected and registered on inclusion: age, sex, body mass index (BMI), body temperature, interval between onset of AC and drainage, comorbidities and coexisting conditions, american society of anesthesiologists (ASA) grade, charlson comorbidity index (CCI), AC grade based on TG 18 severity grading,^[4]^ white blood cell (WBC) count, electrolytes, total bilirubin, C-reactive protein (CRP), and so on. This would systematically reflect the characteristics of participants.

The peri-drainage data would be obtained from 2 hours before drainage to one week after ENGBD or PTGBD, such as drainage success, clinical remission, adverse events, pain scores within 2 hours before drainage and at post-drainage 24 h, 48 h, 72 h, etc.

The following data are collected and registered on peri-LC: gallbladder wall thickness changes (pre-drainage to pre-LC), duration and hemorrhage of LC, gallbladder integrity, drainage tube, hospitalization (hospital stay after gallbladder drainage and cholecystectomy), surgical site infection, severe adhesion, pathology, and LC-related complications.

Results that are negative or undetected or measured as 0 should have corresponding symbolic representation and can not be vacant, in order to distinguish from missing values. The treatment of outliers should be judged from both medical and statistical aspects by the statistician during blind examination.

Images and biological samples including venous blood and bile will be collected for probably ancillary and long-term research. Also, all patients will be followed up 6 months after cholecystectomy.

The volunteers of data acquisition have rich clinical experience and rigorous working attitude, and received training and guidance. Data storage would be carried out by two independent investigators to ensure reliability and validity.

We would also pay attention to and collect the information of the participants who discontinue or deviate before cholecystectomy and the follow-up are completed. To promote participants’ retention and enthusiasm, we would establish workflow manuals contact patients regularly, communicate properly and take effective care of their health.

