#### Analysis

2.14.2

A predefined statistical analysis plan will be followed. All statistical analyses were conducted with IBM SPSS (version 21.0). *P* values of <.05 were considered to represent statistical significance. Categorical variables would be reported as counts and percentages. The mean and standard deviation or median with interquartile ranges (IQR) were used to describe continuous variable data, as appropriate.

The primary analysis is a comparison between ENGBD and PTGBD for the pain remission based on an intention-to-treat principle. A multilevel, random-slope model would be fitted to the data with time points nested in patients to allow for clustering of data within each patient. This model adjusted for the fixed effects of treatment group, time (−2, 24, 48 , or 72 hours), and treatment × time interaction. An unstructured covariance pattern was selected for the repeated measurements as the least restrictive structure, which resulted in better model fit based on log-likelihood values than more constrained patterns. Estimates of the difference in pain scores between treatment groups were assessed overall and at individual time points.

The secondary analysis is a comparison between ENGBD and PTGBD for the rates of technical and clinical success, adverse events, and changes in the gallbladder wall thickness . Also, the outcomes during cholecystectomy including time duration, open conversion would also be analyzed. The Chi-square test or Fisher exact test was used for dichotomous variables, and Wilcoxon test was used for rank data. For quantitative data, two-tailed Student *t* test is used, if the normal distribution and homogeneous total variance are satisfying, otherwise, Wilcoxon test is used.

A blinded adjudication committee will assess the occurrence of the primary and secondary endpoints after the last patient has completed follow-up.

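### The masking stated for the collector of secondary outcomes is not achieved, by the procedures described, for bedside outcomes in the week after drainage

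*Protocol article*

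**What the plan says.** Section 2.13 (Blinding) declares the trial open for patients and physicians "because of the nature of the intervention (position and shape of drainage tube"). It then makes an exception for those who gather and assess the secondary outcomes: "the investigator of collecting secondary outcomes, the assessor of clinical and biological data in charge of statistical analyses and outcome assessment will be masked".

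Three other sections say who does what:

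- Section 2.14.1 (Collection, management): "All data are prospectively collected and managed by the well-trained research volunteers". No exception is made for secondary outcomes.
- Section 2.12 (Allocation sequence generation and randomization): "two volunteers first record the name and the code of the next unopened envelope, then open the envelope and sign their names".
- Section 2.7 (Interventions): "Properly trained volunteers would accompany patients on key treatments, such as ERCP and PTGBD, extubation, LC, etc".

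On timing and content, section 2.14.1 states that "The peri-drainage data would be obtained from 2 hours before drainage to one week after ENGBD or PTGBD", and lists items "such as drainage success, clinical remission, adverse events, pain scores within 2 hours before drainage". Section 2.14.2 (Analysis) makes several of these secondary outcomes: "The secondary analysis is a comparison between ENGBD and PTGBD for the rates of technical and clinical success, adverse events".

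**The concern.** The article promises a masked collector, and then names as collectors a group whose members learn the allocation in two ways: by opening envelopes and by being present at the procedure.

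This matters most where the person recording has to use judgement. Clinical remission is one such outcome. Adverse events are another, because section 2.16 (Harms) records events thought to be related to the trial, and that is a decision made when the event is recorded. The team's expectation is also known: the Introduction presents ENGBD as the safer and less painful option. If the recorder knows the arm, borderline events can be recorded differently in the two groups, and the eventual report would still describe the collection as masked.

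**Working it through.** No arithmetic reproduces or refutes a figure here. The check sets the stated roles and times side by side.

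**Step 1: who collects.** Section 2.13 refers to an investigator who collects secondary outcomes, without saying who that is. Section 2.14.1 is the only place that names collectors of these outcomes, and it names the research volunteers, for all data. The primary pain score is obtained separately by a trained nurse (section 2.8.1).

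**Step 2: who learns the allocation.**

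| Task | Who does it | Section | Does it disclose the arm? |
|---|---|---|---|
| Opening the envelope | Two volunteers | 2.12 | Yes |
| Accompanying at ERCP or PTGBD | Volunteers | 2.7 | Yes, the procedure is the treatment |
| Accompanying at tube removal | Volunteers | 2.7 | Yes, through the tube |
| Collecting and managing data | Research volunteers | 2.14.1 | Stated as masked in 2.13 |

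No section says that the volunteers in the last row are different people from those in the first three.

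**Step 3: would separate people solve it during the peri-drainage week?** The inputs are the collection window (to 1 week after drainage, section 2.14.1) and the tube times (about 4 days for ENGBD, more than 2 weeks for PTGBD, section 2.7).

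- PTGBD: more than 14 days in place against a 7-day window, so the catheter is visible throughout.
- ENGBD, to about day 4: the nasal tube is visible.
- ENGBD, from about day 4 to day 7: the tube is out while PTGBD patients still have theirs, so its absence also points to the arm.

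On each day of the post-drainage window, the bedside view therefore indicates the treatment given. A separate collector at the bedside would still not be masked.

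**Step 4: does the same hold for outcomes around cholecystectomy?** Section 2.7 places cholecystectomy 3 months after drainage. By the stated times both types of tube are out by then, so the argument in step 3 does not apply. Masking then depends only on step 2, that is, on whether the recorder opened that patient's envelope or was present at that patient's drainage or tube removal. It can be achieved with separated roles, but no separation is stated.

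**Step 5: do the later masked layers make up for it?** Section 2.14.2 has a blinded committee assess endpoints after the last patient completes follow-up. It judges what has been recorded. It can reclassify a recorded event, but it cannot recover one that an unmasked collector did not record.

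**The case against.** The strongest counter-argument is that the documents never say the same individuals open envelopes, accompany patients and collect data. The shared word for volunteers does not prove overlap, and section 2.14.1 later refers to those who acquire data by their function, which may mean a subset. This stands. A reader might infer that no masking of collection exists anywhere in the trial, or that every secondary record is made by someone who knows the group. The text does not support either inference. It does not rescue the bedside outcomes, where the tube discloses the arm whoever collects.

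It can also be said that task allocation belongs in a delegation list, which an article may leave out. That is fair for the rota itself. But the article chose to state both the masking and the roles, and the two do not fit.

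Other safeguards are real. The statistician does not know the grouping (section 2.3), outliers are judged at a blind examination and negative results must be coded explicitly (section 2.14.1), and endpoints are adjudicated blind. Explicit coding limits silent gaps, but an event judged not to count would simply be coded as negative.

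The peri-cholecystectomy items give weaker support. Severe adhesion is seen by the surgeon, already declared unblinded as a physician, and operating time, hospital stay and pathology leave the recorder little discretion.

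Finally, a visible tube shows the treatment received, not strictly the assigned arm: section 2.7 allows PTGBD among the alternatives after a failed ENGBD. This blurs the inference for those patients only.

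**Conclusion.** The point holds for bedside peri-drainage outcomes. Section 2.13 states a masking of the collector that sections 2.7, 2.12 and 2.14.1, together with its own remark about the tube, do not deliver. For peri-cholecystectomy items the masking is possible but not secured.

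The size cannot be given as a number, because the documents contain no rate of misrecording and none can be derived. A reader might be tempted to note that one event in an arm of 11 is 1/11 = 9.1 percentage points, and to set this against the gap between the adverse-event rates in the Introduction (14% for PTGBD, 9.3% for ENGBD, so 14 − 9.3 = 4.7 points). That comparison does not measure this problem. One event moves a rate by 9.1 points whether or not the recorder is masked, and the two rates come from different background studies that the trial does not plan on.

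The conclusion assumes that bedside outcomes are recorded by someone who sees the patient, and that tube times are roughly as stated. The primary pain score is outside it: section 2.13 states no masking for the nurse who obtains it. The masking of the statistician and of the adjudication committee is not challenged either. The plan should be corrected, but the primary analysis is not put at risk.

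**What to change.** Reconcile sections 2.7, 2.12, 2.13 and 2.14.1.

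- **Section 2.13:** withdraw the collector-masking statement for bedside peri-drainage outcomes (adverse events, clinical remission, drainage success). Limit it to what can be masked: laboratory values, pathology, coded images, adjudication of records from which the drainage type has been removed, and the statistical analysis.
- **Sections 2.7, 2.12 and 2.14.1:** state that a volunteer who opens a patient's envelope, or accompanies that patient at drainage or tube removal, does not record that patient's later secondary outcomes.

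The second change protects mainly the peri-cholecystectomy items. It will not mask bedside recording in the first week, which is why the first change is also needed. The cost is protocol wording and a rota among existing volunteers. The downside is a less favourable blinding statement in the report, but one that matches what is done.

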### Data collection, management and analysis

2.14

#### Collection, management

2.14.1

All data are prospectively collected and managed by the well-trained research volunteers.

The baseline data would be collected and registered on inclusion: age, sex, body mass index (BMI), body temperature, interval between onset of AC and drainage, comorbidities and coexisting conditions, american society of anesthesiologists (ASA) grade, charlson comorbidity index (CCI), AC grade based on TG 18 severity grading,^[4]^ white blood cell (WBC) count, electrolytes, total bilirubin, C-reactive protein (CRP), and so on. This would systematically reflect the characteristics of participants.

The peri-drainage data would be obtained from 2 hours before drainage to one week after ENGBD or PTGBD, such as drainage success, clinical remission, adverse events, pain scores within 2 hours before drainage and at post-drainage 24 h, 48 h, 72 h, etc.

The following data are collected and registered on peri-LC: gallbladder wall thickness changes (pre-drainage to pre-LC), duration and hemorrhage of LC, gallbladder integrity, drainage tube, hospitalization (hospital stay after gallbladder drainage and cholecystectomy), surgical site infection, severe adhesion, pathology, and LC-related complications.

Results that are negative or undetected or measured as 0 should have corresponding symbolic representation and can not be vacant, in order to distinguish from missing values. The treatment of outliers should be judged from both medical and statistical aspects by the statistician during blind examination.

Images and biological samples including venous blood and bile will be collected for probably ancillary and long-term research. Also, all patients will be followed up 6 months after cholecystectomy.

The volunteers of data acquisition have rich clinical experience and rigorous working attitude, and received training and guidance. Data storage would be carried out by two independent investigators to ensure reliability and validity.

We would also pay attention to and collect the information of the participants who discontinue or deviate before cholecystectomy and the follow-up are completed. To promote participants’ retention and enthusiasm, we would establish workflow manuals contact patients regularly, communicate properly and take effective care of their health.

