### Harms

2.16

All adverse events thought to be related to the trial would be recorded rigorously and carefully. Any unexpected major serious complications suspected to be associated with ENGBD must be reported to interviewer and attending physicians, the trial may be temporarily stopped, and effective treatment measures in the first place will be taken by attending physicians.

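### The named adverse-event window closes one week after drainage, before PTGBD tube removal; it is not reconciled with the Harms section, whose serious-complication reporting sentence names only ENGBD.

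*Protocol article*

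**What the plan says.** All references are to the protocol article.

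- **Collection window (2.14.1).** Peri-drainage data start 2 hours before the procedure and run "to one week after ENGBD or PTGBD, such as drainage success, clinical remission, adverse events". The same limit applies to both arms.
- **Tube times (2.7).** The ENGBD tube comes out when the bile clears, "which is approximately 4 days after the drainage based on our experience". For the comparator, "PTGBD group extubate after more than 2 weeks due to fistula formation".
- **Surgery (2.7).** The rule is the same in both arms: "we require all patients to undergo cholecystectomy 3 months after drainage".
- **Harms (2.16).** The recording rule has no limit by time or arm: "All adverse events thought to be related to the trial would be recorded rigorously and carefully". The next sentence is narrower: "Any unexpected major serious complications suspected to be associated with ENGBD must be reported to interviewer and attending physicians". It adds that the trial may be paused.
- **Use of the data (2.14.2).** "The secondary analysis is a comparison between ENGBD and PTGBD for the rates of technical and clinical success, adverse events". Section 2.8.2 presents the secondary measures as a comprehensive picture of the effectiveness and safety of drainage.
- **Later collection (2.14.1).** The peri-cholecystectomy list contains surgical items, including surgical site infection and LC-related complications. Follow-up 6 months after surgery is planned, without stated content.

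**The concern.** The two drains stay in for very different times. A window that ends on day 7 follows a typical ENGBD patient through the whole tube period, removal and a few days more. A PTGBD patient leaves the same window with the tube still in place. The Introduction's own list of PTGBD complications includes inadvertent removal, which can occur on any day the tube is in, and bile leak peritonitis. Events of this kind after day 7, or at planned removal, fall outside the period in which 2.14.1 says adverse events are gathered.

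Section 2.16 could pick them up, but it uses a different criterion (suspected relation to the trial) and a different, open-ended period. The protocol does not say which set of events enters the comparison in 2.14.2. Two analysts could follow the text faithfully and produce different adverse-event rates, with the difference falling mainly on the PTGBD arm.

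The serious-complication sentence is a separate matter. Section 2.15 dispenses with a monitoring committee and interim safety analysis, so this sentence is the only stated trigger for prompt reporting, and as worded it does not cover a serious complication of PTGBD. It also leaves unclear how to treat a patient allocated to ENGBD who receives PTGBD as the alternative procedure allowed in 2.7.

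**Working it through.** **Inputs**

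- Window: 7 days after drainage, both arms (2.14.1).
- Tube in place: ENGBD about 4 days; PTGBD more than 14 days (2.7).
- Background adverse-event rates: PTGBD up to 14%, ENGBD 9.3% (Introduction).
- Patients: 11 per arm (2.10).
- Not given anywhere: the share f of PTGBD events that occur after day 7. It is treated as an assumption and varied.

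The protocol states no figure for its own safety comparison, so there is none to reproduce.

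**Step 1. Share of tube time inside the window** = min(7, tube days) / tube days.

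- ENGBD: 4/4 = 100%, with 7 − 4 = 3 days left after removal.
- PTGBD: 7/14 = 50% as an upper bound, because the tube stays in for more than 14 days. If it stayed 21 days, 7/21 = 33%; if 28 days, 7/28 = 25%.
- Planned PTGBD removal, after day 14, is never inside the window.

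**Step 2. Effect on the observed PTGBD rate.** Assume that all ENGBD events are captured and that the cited 14% refers to the whole tube period. Then observed PTGBD rate = 14% × (1 − f).

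| Share of PTGBD events after day 7 (f) | Observed PTGBD | Minus ENGBD 9.3% |
|---|---|---|
| 0 | 14.0% | +4.7 points |
| 25% | 10.5% | +1.2 points |
| about 34% | 9.3% | 0 |
| 50% | 7.0% | −2.3 points |
| 75% | 3.5% | −5.8 points |

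The break-even share is 1 − 9.3/14 = 0.336. The 50% row is what an even spread over 14 days would give.

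**Step 3. What 11 per arm can show.** Expected events are 11 × 0.14 = 1.54 for PTGBD and 11 × 0.093 = 1.02 for ENGBD. For power (two-sided 5%, normal approximation), the mean rate is 0.1165.

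- Null standard error: √(2 × 0.1165 × 0.8835 / 11) = 0.137.
- Alternative standard error: √((0.14 × 0.86 + 0.093 × 0.907) / 11) = 0.136.
- Power: Φ((0.047 − 1.96 × 0.137) / 0.136) = Φ(−1.62), about 5%.

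This is no better than the significance level itself.

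**Step 4. Direction.** Losing PTGBD events makes PTGBD look safer, so the truncation works against ENGBD. Its size depends on f and cannot be derived from the document.

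**The case against.** The strongest reply is that the window is identical in calendar time for both randomized groups, so a comparison of 7-day event rates is not biased as such. That stands. The difficulty arises only when the result is read as the safety of the drainage, which is how 2.8.2 frames the secondary measures.

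A reader might infer that adverse events are collected for one week only. The document does not support this. Section 2.16 records trial-related events in both arms without a time limit, and 2.14.1 adds LC-related complications, regular contact and later follow-up. A tube complication on day 10 can be recorded under 2.16. What remains is that the two sections are not reconciled.

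A reader might also infer that ENGBD events will be over-counted because the serious-complication sentence names that arm. It governs reporting and a possible pause, while the recording sentence before it is neutral between arms. Section 2.16 does not say who judges relatedness. Section 2.13 masks the collector of secondary outcomes, and 2.14.2 provides a blinded adjudication committee. Nor would such over-counting offset the window: under-counting PTGBD and over-counting ENGBD would both disfavour ENGBD.

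Finally, several PTGBD complications in the Introduction, such as bleeding, pneumothorax and catheter misplacement, plausibly occur at or near insertion, which would keep f low. The 14% is also quoted as an upper figure with no time frame. Both cautions stand, which is why a range is shown. Tables 1 and 2 are not available here and may define adverse events or their schedule; the list in 2.14.1 is itself illustrative.

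**Conclusion.** The point holds as a gap in safety ascertainment that should be fixed. It does not touch the primary pain outcome. As written, the named adverse-event window covers the typical ENGBD tube period in full, at most half of the PTGBD tube period, and not the planned PTGBD removal. It is not reconciled with the open-ended recording rule in 2.16, and the serious-complication reporting sentence covers one arm only.

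If the one-week data are read as the safety of the drainage, PTGBD events may be under-counted, to the disadvantage of ENGBD. With the cited background rates, the observed PTGBD rate would lie between 14.0% (no late events) and 7.0% (half of them late). It would equal the ENGBD rate when about 34% are late. This rests on the assumptions that all ENGBD events are captured and that 14% and 9.3% apply to this population and to the whole tube period.

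A reader might conclude that the ranking of the two methods would be reversed. The document gives no timing of events to support that, and with roughly 1.5 against 1.0 expected events the observed order means little either way. The comparison is descriptive.

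**What to change.** 1. **Sections 2.14.1 and 2.16:** state one adverse-event window for both arms that extends past PTGBD tube removal. The simplest choice is from the start of the allocated procedure to cholecystectomy. Record events in the same way in both arms, regardless of suspected relationship, and say that this set feeds the comparison in 2.14.2.
2. **Section 2.16:** word the serious-complication reporting sentence so that it applies to either group.
3. **Tables 1 and 2:** check that the adverse-event definition and the participant timeline agree with the revised window.

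None of this changes treatment. The cost is wording in two sections and somewhat more case-report work up to surgery. Part of the contact already exists: 2.7 has volunteers accompany patients at extubation and surgery, and 2.14.1 plans regular contact. The change is best made while recruitment is open, because events between day 7 and surgery that were not recorded at the time are hard to recover later.
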